## 9 Sensitivity analyses

Our audit occurred retrospectively and in some cases many months after the patient’s operation, which had two main effects on data quality. First, roughly half the patients were lost to follow-up, a much larger proportion than expected. Second, simply by the circumstances of field work, the patients in the control group had longer recall periods than the intervention group, introducing a differential recall bias by arm. We address both issues with sensitivity analyses.

### 9.2 Sensitivity to fieldwork staff

In our original follow-up data collected by the data collectors, one hospital had an SSI rate around 9%, which is compatible with national reports of SSI data. Our first sensitivity analysis will be to run the main model predicting SSI but include the follow-up data according to the data collectors for this single hospital rather than the data collected by the auditors.

### 9.3 Sensitivity to hospitals

Our second sensitivity analysis will be to serially exclude each individual hospital from our dataset to demonstrate how individual hospitals may be driving outcomes. We will use the aggregate of all nine hospitals as our main result regardless of this outcome but will report if any one hospital appears to be driving results in our manuscript or in an appendix. Variation between hospitals is anticipated because this study is a behavioral intervention rather than a physiologic one. It can have differing effects based on intangible differences in culture and leadership at hospitals. If one hospital is significant driving results, we anticipate that we will pursue post-hoc analyses to understand why that hospital may be different.

### 9.4 Sensitivity to loss to follow-up

First, we will construct a demographic table comparing the women who were followed up by the auditors against those who were not. This may identify some imbalances that may introduce bias.

Next, we will use multiple imputation methods to model the primary outcome with the total CS population. We will generate an imputed value and 95% CI for the OR of SSI in the intervention versus control period.

### 9.5 Sensitivity to recall bias

For the audited results, we expect that patients in the control condition had to recall further back in time compared to the intervention patients. This may bias our results if longer recall periods lead to underreporting of forgotten SSI events.

First, using the CS population with follow-up, we will calculate the number of days between the operation and an auditor's follow-up call that succeeded in capturing the SSI data. We will report means, medians, and IQRs across the arms, as well as construct histograms of this follow-up time. This will show by how many days the recall period differed across arms.

Next, we will calculate the SSI rate by month of this recall time, in the control condition only. We expect to see the SSI rate decline at the longer recall periods, allowing us to assess the degree of suppression introduced. We focus here on the control condition because the results from the intervention condition may be confounded by lower SSI rates due to the impact of the intervention rather than faulty recall.

These steps will allow us to assess the bias likely introduced by any differences in recall. We expect that any bias will be conservative against our intervention, since it will likely suppress SSI rates in the control condition more than the intervention, making it more difficult for the study to detect an effect of the intervention. This may help us interpret the results of aim 1.

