## 4. Audit of 30-day follow-up data

### 4.1. Background

In May 2022 the study team became concerned that SSI rates at 30-day phone follow-up were too low relative to lived experiences of Ethiopian clinicians and published data on SSI rates in Ethiopia following caesarean section, calling into question the quality of the follow-up data. We were concerned the data collectors were missing a significant number of SSI on 30-day follow-up. Although we had robust in-hospital SSI data, most SSIs occur after hospital discharge, and total (inpatient and 30-day) SSI rate is the primary outcome of this study. For these reasons, we decided to audit outcomes on the entire sample using staff with more clinical and research training. Beginning in August 2022, we recruited and trained general practitioners on the 30-day follow-up data collection tool, and between September 2022 and March 2023, these auditors called all patients and re-collected 30-day follow-up data retrospectively. The original set of data collectors continued to collect follow-up data as well.

In this SAP, we refer to the initial group of workers whose data was called into question as the “data collectors,” and the more trained workers who replicated the follow-up calls as the “auditors.”

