**Figure 1. SSI rates as measured by data collectors and auditors, by hospital**

Among 5,093 live births that occurred pre-intervention (control condition) and pre-audit launch, defined as September 1, 2022.

[figure not shown]

Given the literature, we expect that Ethiopian hospitals in the control condition will show some variation in SSI rates, forming a roughly normal distribution about a mean of 9% to 12%. The data from the auditors (right hand axis in figure 1) appears much more likely to have been drawn from this distribution. The one hospital below 3% is concerning for undercounting infections, but not impossible.

The data collected by auditors is subject to recall bias, as they were collected up to a year after the birth. A study on recall bias in Ethiopian women undergoing caesarean section showed that women are less likely to report complications the further they recede in time. In our circumstances, this means that the auditor's data likely underestimates the SSI, since they required longer recall. Since the auditors began in September 2022, most of the cases with long-term recall were in the control condition, which would lower the baseline estimate of SSI. This biases the data against rejecting the null hypothesis, which is a conservative bias.

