## 7. General statistical considerations

### 7.1. Modeling

As stated in our protocol, we will use the statistical approach recommended by Hemming and colleagues. To estimate how the intervention is correlated with outcomes, we will fit a mixed effects logistic regression model of the form:

$$Outcome_{ij} = \beta_0 + \beta_1 Month + \beta_2 Intervention + \beta_x X + \mu_i + \varepsilon_{ij}$$

Where:

|                       |                                                                                                                                                     |
|-----------------------|-----------------------------------------------------------------------------------------------------------------------------------------------------|
| Outcome ij | Binary variable for the j th patient in the i th cohort, where 1 = had the adverse outcome, and 0 = did not have the outcome. |
| Month                 | Fixed categorical variable with 18 levels, one for each month. Reference category will be either the first or last month of the study.              |
| Intervention          | Fixed binary variable, where 1 = procedure occurred under intervention condition, 0 = procedure occurred under control condition.                   |
| X                     | Vector of fixed demographic and clinical controls                                                                                                   |
| β 0-x      | Set of regression coefficients                                                                                                                      |
| μ i        | Random effect for cohort                                                                                                                            |
| ε ij       | Error term for the j th patient in the i th cohort                                                                            |

Since this is a cross sectional design (no repeated measures on patients over time), we will not need to account for patient-level correlation over time. The random effect for cohort will account for the within-cluster variance, assuming one shared ICC. We will consider adding a random cohort-by-month interaction term, which would allow for different within-period and between-period ICCs.

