Our estimate of interest is  $\exp(\beta_2)$ , the exponentiated coefficient for the intervention period, which will express the odds ratio (OR) of having the outcome after the intervention started versus beforehand.

Note: In our pilot work, we modeled the surgical infection outcome with a modified Poisson regression, specifying a Poisson distribution for the binary outcome with a log link and robust

error estimation. This method directly estimates relative risks (RR) rather than ORs, which can overestimate RRs when the baseline risk is high. However, in this case we believe the baseline risks are low enough as to not require this correction. Further, the pilot was an uncontrolled pre-post study, and for the current analysis we will adhere to the standard logistic mixed effects approach for randomized stepped wedge trials, as stated in our protocol.

Because we cannot tell with complete certainty the differences between hospitals or the effects of sociopolitical factors in Ethiopia during this time, we will also model our primary outcome using generalized estimating equation (GEE) as a sensitivity analysis to assess whether any alternative model would better assess the outcomes of this study. While we do not necessarily anticipate large differences in results between models, if we do find differences in magnitude or significance of the effect of the intervention in a GEE framework versus mixed effects, we will pursue further analysis to dissect what may be driving those differences.

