## **10 Limitations**

Because we are opting to use data collected by auditors retrospectively up to one year after the enrolled patient’s initial operation, a key limitation in our study is recall bias. In a prior study assessing the roll of recall bias in evaluating complications after surgery in Ethiopian woman undergoing caesarean section, women were less likely to recall complications 6 months after their operation. As a result, our study cohort is more likely to remember complications at the end of the study, after the intervention, than at the beginning of the study before the intervention, in the control period. We believe this limitation is likely to bias us against finding a reduction in SSI associated with our outcome.

Additionally, loss to follow-up is a major limitation. Nearly half of patients could not be reached for their 30-day follow-up phone call by the auditors. However, in comparing demographic and clinical characteristics of these patients, they were not substantively different from our complete dataset. Sensitivity analyses to address loss to follow-up are described in Section 9.4.

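### The SAP calls recall bias in Aim 1 conservative, but that argument fits a crude arm comparison, not the month-adjusted odds ratio, whose residual recall bias has unknown direction and may be near zero

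*Combined protocol and SAP*

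**What the plan says.** SAP 4.1 gives the timing of the audit: "between September 2022 and March 2023, these auditors called all patients and re-collected 30-day follow-up data retrospectively". The SAP then argues three times that the resulting recall problem works against the intervention.

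- Section 4.2: "Since the auditors began in September 2022, most of the cases with long-term recall were in the control condition", and from this, "This biases the data against rejecting the null hypothesis, which is a conservative bias".
- Section 9.5: "We expect that any bias will be conservative against our intervention, since it will likely suppress SSI rates in the control condition".
- Section 10: "We believe this limitation is likely to bias us against finding a reduction in SSI associated with our outcome".

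Each time the reason is that control operations came earlier. Section 7.1 defines the Aim 1 estimate differently from a comparison of arms. It is exp(β2) from a logistic mixed model in which month is a "Fixed categorical variable with 18 levels, one for each month" and clustering enters as a "Random effect for cohort". The SAP does not connect the two.

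Section 9.5 plans to summarise recall time by arm, and then SSI rate by recall month in control women only. It does not compare recall within operation month or cohort, and it does not put recall time in the model. No section says in what order the auditors called cohorts, hospitals or arms.

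**The concern.** Recall length is the call date minus the operation date. All calls fell in one seven-month window, so recall depends largely on the month of operation, and the model has a term for every such month. The pooled arms differ greatly in recall. Women in different arms operated on in the same month need not differ at all. A bias argued from the pooled arms is therefore not a property of the adjusted OR.

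Section 9.5 says that its recall checks might inform how Aim 1 is read. With the conservative label attached, a reader could discount a null result, or treat a positive one as an underestimate, on grounds that do not apply to the reported estimate. If call order favoured the intervention, the label would hide a bias in the other direction.

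**Working it through.** **1. The SAP's own figures.** The Table 4 follow-up rates reproduce: 2,764/5,715 = 48%, 2,828/4,951 = 57%, and 5,592/10,666 = 52%. (Table 3 prints a total of 5,525, but its two arms sum to 2,764 + 2,828 = 5,592. This does not affect the point.) The SAP gives no figure for the size of the recall bias.

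**2. Why month terms matter.** Let f(R) be the share of true SSIs still reported after recall R = call date − operation date.
- If the call date does not depend on cohort or arm, given operation month, then R and f(R) depend on month alone. The loss falls into the month coefficients, not β2.
- If cohorts were called at different times, R differs between cohorts within a month. A constant cohort shift with log-linear loss is largely taken up by the cohort term. A stepped loss, or calls that could not precede day 30, leaves a remainder in β2.
- If call timing differed by arm within a month, the difference goes into β2 directly.

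**3. Inputs for a numerical check.** From the SAP: audited counts by cohort (control 111, 422, 600, 783, 848; intervention 545, 851, 603, 607, 222), the launch dates in Table 2, and the call window September 2022 to March 2023. From the protocol's power section: 12% control SSI. Assumed:
- a 35-day run-in (the SAP says four to six weeks);
- operations spread evenly over days, and no call before day 30;
- no inpatient share unless stated;
- the recall curves and call schedules.

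Reported probability = true probability × f(R). I fitted a large-sample logistic model with intervention, month and cohort, the last as fixed effects.

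**4. Recall by arm and by month.** With calls spread evenly over the window, mean recall is about 11.2 months in control women and 3.4 to 3.8 in intervention women, depending on how late calls are handled. Within a month it is nearly equal: 10.0 against 10.0 in February 2022, and 5.1 against 5.0 in July 2022. About 2,410 of 5,592 audited women (43%) were operated on in months containing both conditions. The adjusted contrast rests mainly on them.

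**5. Calls unrelated to cohort and arm, true OR 1.0.** Without month terms (cohort-adjusted), recall loss alone gives an OR of about 1.4 to 2.7, which is the bias the SAP describes. With month terms it gives 1.00 to 1.02.

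**6. Month-adjusted OR when the true OR is 0.719** (12% against about 8.9%):

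| Call schedule | Reporting halves per 12 months | Halves per 6 months | Step to 60% after 6 months |
|---|---|---|---|
| Even, alike at all hospitals | 0.73 | 0.74 | 0.73 |
| In order of operation date | 0.73 | 0.74 | 0.74 |
| By cohort, launch order | 0.78 | 0.86 | 1.07 |
| By cohort, reverse order | 0.69 | 0.64 | 0.60 |

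For the first row and the 12-month half-life, the crude OR is 1.17. The shift in the first two rows is at most 0.74/0.719 = 1.03. Part of it is the OR moving towards the risk ratio (0.089/0.12 = 0.74) as reported events become rarer.

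**7. True OR 1.0 with ordered calls.** Ordering by cohort gives 0.78 to 1.49, and ordering by arm within operation month gives 0.74 to 1.37.

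**8. Precision.** Power ≈ Φ(|ln 0.725|/SE − 1.96), where 0.725 is the OR for 12% against 9%. Recall loss raises the SE of the log OR from about 0.185 to 0.218. Power is Φ(0.3216/0.185 − 1.96) = 41% before and Φ(0.3216/0.218 − 1.96) = 31% after.

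**9. Adding recall to the model** (true OR 0.719). A linear term recovers 0.72 to 0.73 under the two half-life curves. Under the step it gives 1.06 (launch order) and 0.62 (reverse). Three-month categories give 0.72 to 0.73 under the step, but 0.76 and 0.71 under the 12-month half-life.

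**The case against.** The SAP is hedged. It speaks of expectation and likelihood, and the Aim 1 decision rule in 8.2 does not use recall at all. A reader might infer that the sponsor will excuse a null or inflate a positive result. The documents do not say so, and this remains a possibility only.

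A reader might also infer that month terms always absorb the recall difference. They do not: they capture operation date, not call date, and call order is undocumented. Some orders leave a bias in the SAP's direction, and launch order is one.

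Nor do the documents show a false benefit. The reverse-order schedule is hypothetical, and it is strained for the last cohorts, whose intervention operations mostly fall after their calling block. Inpatient SSIs need no recall. If they made up 30% of events (assumed), the reverse-order estimates for a true OR of 1.0 under the half-life curves move from 0.94 and about 0.87 to 0.96 and 0.92. Even spreading also implies recall of up to about 20 months, whereas the SAP speaks of up to a year. Calling in order of operation date has a maximum of about 13 months and gives the same answer.

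It is tempting to add that the SAP contradicts itself by accepting auditor rates near 9-12% while calling them suppressed. It does not. It calls them more plausible than the data collectors' rates, flags one hospital for possible undercounting, and admits measurement problems in both sources.

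What stands of the objection is that lost recall does make an effect harder to detect. That is loss of precision, not bias in the OR.

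**Conclusion.** The concern holds in limited form. The three directional statements describe a crude arm comparison, and the SAP gives no argument that they apply to the month- and cohort-adjusted OR. If call timing was unrelated to cohort and arm, residual recall bias is about 0-3% of the OR in the scenarios tested. If it was related, the bias can run either way and can be material.

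The sizes rest on assumed recall curves, call schedules and inpatient share, and on audited counts that trace to all enrolled operations, whereas Aim 1 is cesarean only. They also use fixed cohort effects. Random-intercept fits with equal cohort baselines agree (1.00 to 1.01 for a true OR of 1.0 when calls are unrelated to cohort and arm). With unequal assumed baselines the random-intercept fit gave 0.93 even with no recall loss, so that shift is not a recall effect. The logical point needs none of these assumptions.

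**What to change.** - In 4.2, 9.5 and 10, replace the directional statements with: after month adjustment, the direction of any residual recall bias is unknown and may be near zero; lost recall also reduces precision.
- In 9.5, tabulate days from surgery to the successful auditor call by condition within operation month and cohort, in addition to the pooled arms. This would show whether call timing depended on cohort or arm.
- Do not read a falling SSI rate by recall month in control women as proof of suppression. Among them recall is close to calendar time reversed, and cohort mix changes: cohort 1 contributes controls only to late December 2021, cohort 5 to September 2022.
- As a sensitivity analysis, refit Aim 1 with recall time in a flexible form (3-month categories or a spline). A linear term may be shown too, but not alone. Report the ORs beside the primary one.

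**Cost.** Wording, one table and one or two fits on recall days that 9.5 already computes. No form of recall term is safe under every curve (step 9 of the working), so the refit shows sensitivity and does not correct the estimate. A linear term raised the SE by 0-9%. Three-month categories can cost far more when calls were ordered by cohort: under the step curve the SE went from 0.214 to 0.362 (0.362/0.214 = 1.69) in launch order and from 0.211 to 0.234 (1.11) in reverse. A reassuring sentence is lost. The primary analysis does not change.

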### 9.4 Sensitivity to choice of model

In our primary analysis (aim 1), we will use mixed effects logistic regression, fitting random intercepts for each of the five cohorts, which are defined in tables 2 and 3 above. This accounts for our hierarchical data with a random effect, so we will interpret the resulting ORs as the estimated effect of CLEAN-CUT implementation on the individual patient level (known as subject-specific or conditional estimates). An example interpretive sentence might be: “In our study, individuals who underwent a CS after CLEAN-CUT implementation were X% less likely to develop an SSI.”

In this sensitivity analysis of our primary aim, we will use a generalized estimating equation (GEE) framework with the same data. One strength of GEE is its accommodation of repeated measures of individual patients over time. While we do not measure patients repeatedly in our study, one view of our data is that the operating theater and team are measured repeatedly over time. Under this view, we will treat cohort as the unit of repeated measure in the GEE, using an autoregressive covariance structure, which assumes the strongest correlations between adjacent time periods and systematically decreasing correlations with increasing distance in time.

This accounts for our hierarchical data with repeated measures, so we will interpret the resulting ORs as the estimated effect of Clean Cut implementation on the population level (known as marginal effects). An example interpretive sentence might be: “For the hospitals in our study, the population of CS patients was X% less likely to develop an SSI after the implementation of Clean Cut.”

The difference in interpretation between ME and GEE is fairly subtle, and in most applications their estimates are similar. In the event that the magnitude or significance of the OR differs in our data between these models, then we will investigate further the pattern and magnitude of clustering effects to identify the cause of the differences.

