### 1.2. Multiple comparisons

This analysis includes 6 aims, which collectively involve fitting 12 models (Table 7). Each model has a single predictor of interest, which is the intervention variable in all models except in aim 6, where the predictor of interest is the flag for high-compliance surgeries. We will evaluate each p value against an alpha of 0.05 and will not adjust for multiplicity.

Table 7: Number of planned models across all aims

|            |       |                                                | N models |
|------------|-------|------------------------------------------------|----------|
| Primary    | Aim 1 | Infection reduction in CS                      | 1        |
| Secondary  | Aim 2 | 6 compliance domains, 1 overall score          | 7        |
|            | Aim 3 | Reduced maternal postoperative mortality       | 1        |
|            | Aim 4 | Reduced neonatal mortality                     | 1        |
| Additional | Aim 5 | SSI, maternal mortality, or neonatal mortality | 1        |
|            | Aim 6 | Compliance, surgical infection                 | 1        |

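### The five-cluster GEE sensitivity analysis names no variance estimator or small-sample correction; with the usual uncorrected sandwich and normal reference it would reject a true null roughly 18–30% of the time

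*Combined protocol and SAP*

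**What the plan says.** SAP section 7.1 (Modeling) sets a mixed effects logistic model as the primary analysis, with month entered as a "Fixed categorical variable with 18 levels, one for each month" and a random effect for cohort. It then adds: "we will also model our primary outcome using generalized estimating equation (GEE) as a sensitivity analysis". The stated aim is "to assess whether any alternative model would better assess the outcomes of this study".

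SAP section 9, Sensitivity to choice of model (the second of two subsections printed as 9.4), describes the primary analysis as "fitting random intercepts for each of the five cohorts" and the GEE as follows: "we will treat cohort as the unit of repeated measure in the GEE, using an autoregressive covariance structure". It explains the structure as strongest correlation between neighbouring time periods, fading with distance in time, and says the data are the same as in the primary model. If the size or the significance of the odds ratio differs between the two models, the clustering will be investigated further.

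On testing, the SAP says: "We will evaluate each p value against an alpha of 0.05 and will not adjust for multiplicity". Neither section states a variance estimator, a small-sample correction or a reference distribution for the GEE. The one mention of robust errors is about the pilot study's model, "specifying a Poisson distribution for the binary outcome with a log link and robust" errors, and not about this one.

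**The concern.** The usual GEE variance, the sandwich, is justified when there are many independent clusters. Here there are five. If the primary mean model carries over, there are 19 coefficients before the eight patient-level controls: an intercept, 17 month contrasts and the intervention. With so few clusters the uncorrected sandwich tends to be too small, and a normal reference makes this worse.

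The SAP gives the comparison of significance a role. A falsely significant GEE could be read as support for a weak primary result, or could set off a search for reasons behind a disagreement that is only an artefact. About half of the patients have no audited follow-up (SAP Table 4), so readers will lean on the sensitivity analyses more than usual.

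**Working it through.** **Figures in the plan.** The documents give no error rate for the GEE. The protocol's planned total, from 80 to 90 patients per cluster per month, reproduces: 80 × 5 × 18 = 7,200 and 90 × 5 × 18 = 8,100. The condition totals in SAP Table 3 also reproduce: 111 + 422 + 600 + 783 + 848 = 2,764 control and 545 + 851 + 603 + 607 + 222 = 2,828 intervention, 5,592 together. The N column of that table sums to 5,525; the condition counts were used.

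**Rank.** The sandwich is H⁻¹(Σ SᵢSᵢᵀ)H⁻¹, where Sᵢ is the score sum of cohort i. At the solution the five score sums add to zero, so the middle matrix has rank at most 5 − 1 = 4, against 19 coefficients.

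**Simulation under a true null (OR = 1).**
- From the documents: five cohorts, 18 months, Table 3 counts, a baseline SSI rate of 9% or 12% (SAP 4.2).
- Assumed: counts spread evenly over months; the four-to-six-week run-in (SAP 3.2) taken as one missing month; latent ICC 0, 0.01, 0.05 or 0.15 (0.15 is the protocol's planning example); cluster effects constant or decaying over time; tests two-sided; the eight controls omitted.
- Main simulation: logit-link GEE on cohort-month cells with month categories plus intervention, 1,000 data sets per setting. Near a rate of 25% the Monte Carlo error is √(0.25 × 0.75 / 1,000) = 1.4 points.
- Two separately coded simulations with an independence working structure, 600 and 1,500 data sets per setting, served as checks.

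| Variance and reference | Rejection of a true null at nominal 5% |
|---|---|
| Uncorrected sandwich, normal: AR(1) by month | 23–27% |
| Uncorrected sandwich, normal: independence | 23–28% |
| Same, first check: month categories / linear month | 25–29% / 18–26% |
| Same, second check | 22–30% |
| Uncorrected sandwich, t(4): AR(1) by month | 11–15% |
| Uncorrected sandwich, t(4): checks | up to 17%; 9–12% with linear month |
| Model-based with estimated scale, AR(1) by month | 5–9% |
| Mancl-DeRouen, normal: AR(1) by month | 6–9% |
| Mancl-DeRouen, t(4): AR(1) by month | 2.5–4.0% |

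In the first check the true standard error was 1.3 to 1.7 times the mean reported sandwich error. The inflation does not need a large ICC: at ICC 0 the sandwich with a normal reference rejected 22% (9% SSI) and 23.5% (12% SSI).

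**Within-month correlation.** There are about 5,592 / (5 × 17) = 66 patients per cohort-month, and the SAP does not say how patients in the same month are correlated. If model-based errors were used and clustering were in effect ignored (approximated by independence), rejection was 14–18% at ICC 0.01, 36–44% at 0.05 and about 64% at 0.15. The 5–9% for model-based errors in the table therefore depends on a cell-level fit that the SAP does not state.

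**The case against.** The strongest reply is that the SAP does not say the errors are robust, so no single error rate belongs to the plan. That stands. Across standard choices for the AR(1) fit the rate runs from about 2.5% to 27%, and a reader who takes 22%, or any one figure, as a property of the plan goes beyond the text.

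A reader might also infer that the autoregressive structure is at fault, because on patient-level data it would fade within a few patients. The documents do not support this. The SAP ties the correlation to time periods, not to patient order, and in simulation the inflation is as large or slightly larger under independence. What is missing is the correlation within a month.

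A third tempting reading is that a five-cluster GEE cannot serve as a robustness check at all. The same fit with a small-sample correction and t(4) keeps its error below 5%, so it can be repaired.

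The consequence is also bounded. SAP 8.2 rests the aim 1 conclusion on the primary model, and a disagreement leads only to further investigation. No rule lets the GEE override the primary result. The alpha statement is made about the 12 models of Table 7, which does not list the GEE; its use here is an inference from the planned comparison of significance.

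Finally, the inputs are illustrative. Table 3 is not labelled as cesarean patients only, and the mean model of the GEE is not restated. Neither is likely to change the order of magnitude.

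What remains is more than missing detail: run in the usual way, the analysis gives an invalid p value and confidence interval.

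**Conclusion.** The point holds in conditional form. The SAP compares the significance of a five-cluster GEE with the primary model and does not say how that significance will be calculated. With an uncorrected sandwich and normal reference, type I error is roughly 18–30%, or four to six times nominal; with t(4) alone it is about 10–17%. With a bias-corrected sandwich and t(4) it is about 2–4%. These figures rest on the Table 3 counts, an even spread over months, the assumed ICCs, and a mean model without the patient controls. The driver is the number of clusters. This should be corrected before the analysis is run, but it bears on a sensitivity analysis and does not by itself undermine the primary conclusion.

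**What to change.** In the SAP section on sensitivity to choice of model:

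1. Keep cohort as the cluster, since the hospital pair is the unit whose order was randomised (protocol, Site randomization). Moving to nine hospitals to gain clusters would treat paired hospitals as independent. Coarsening time to calendar quarters would put the launches of 11 July and 13 September 2022 in one period.
2. State that the autoregressive correlation is indexed by month, and give the correlation assumed between patients in the same cohort and month.
3. Use a bias-corrected sandwich (for example Mancl-DeRouen) with a t reference on 5 − 1 = 4 df for both the p value and the interval.
4. Add a permutation test of the intervention coefficient over the 5! = 120 cohort orders; the smallest attainable p is 1/120 = 0.008. SAP 3.1 says that only launch order was randomised and that cohorts had some choice of date. So hold the achieved launch dates and run-in gaps fixed to positions in the sequence, state this as an assumption, and say how months that fall in a reassigned gap are handled. The achieved launches were 63, 69, 63 and 64 days apart (SAP Table 2), so the assumption is plausible.

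The cost is a paragraph of SAP text and a short program. The downside is a slightly conservative test and wider intervals: the t(4) multiplier alone is 2.776 / 1.960 = 1.42 times the normal one, before the bias correction.
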